**FIGURE 2 F2:**
[figure not shown]
Base-peak chromatogram (BPC) of MSNP. **(A)** Negative-ion scan. **(B)** Positive-ion scan.

### Outcomes

2.6

#### Primary outcome

2.6.1

The primary outcome of this trial is the total effective rate at the end of the 6-week treatment period, defined as the proportion of participants achieving a ≥25% reduction in their HAMD-17 total score from baseline (Wang et al., 2019). The HAMD-17 is an observer-rated instrument designed to assess depressive symptoms in individuals with a clinical diagnosis of depression. According to standard thresholds, a HAMD-17 score of 0–7 indicates no depression, 8–16 indicates mild depression, 17–23 indicates moderate depression, and ≥24 indicates severe depression (Zimmerman et al., 2013). Treatment response is categorized into four groups based on the percentage reduction in HAMD-17 scores from baseline: recovery (≥75% reduction), markedly effective (≥50% reduction), improved (≥25% reduction), and ineffective (<25% reduction) (Wang et al., 2019). The total effective rate is defined as the proportion of participants classified as recovered, markedly effective, or improved.

#### Secondary outcomes

2.6.2

Change from baseline in HAMD-17 total scores. Assessments will be performed at baseline, during the treatment phase (Weeks 2, 4, and 6), and at the Week 10 follow-up visit.Depression remission rate at the end of the 6-week treatment period, defined as the proportion of participants achieving a HAMD-17 total score of ≤7 (Zhao et al., 2019).Change from baseline in Patient Health Questionnaire-9 (PHQ-9) total scores. The PHQ-9 is a self-administered tool used to assess the severity of depressive symptoms over the past 2 weeks. It consists of 9 items, each scored from 0 to 3, with total scores ranging from 0 to 27. Scores of 0–4 are considered normal; 5–9 indicate mild depression; 10–14, moderate depression; 15–19, moderately severe depression; and 20–27, severe depression (Sun et al., 2020). Assessments will be conducted at baseline and at Weeks 2, 4, 6, and 10.Proportion of participants requiring an increased dosage of paroxetine during the 6-week treatment period.Change from baseline in Generalized Anxiety Disorder-7 (GAD-7) total scores. The GAD-7 is a self-reported screening and assessment tool for anxiety symptoms over the past 2 weeks. It consists of 7 items scored from 0 to 3, with total scores ranging from 0 to 21. Higher scores indicate greater anxiety severity, with a score ≥10 is generally considered clinically significant (Aktürk et al., 2025). Assessments will be performed at baseline, and at Weeks 2, 4, 6, and 10.Change from baseline in Pittsburgh Sleep Quality Index (PSQI) total scores. The PSQI assesses sleep quality over the past month across seven domains, each scored from 0 to 3, with total scores ranging from 0 to 21. Scores of 0–5 indicate very good sleep quality; 6–10, good; 11–15, average; and >15, poor sleep quality (Wang et al., 2024). Assessments will be performed at baseline, and at Weeks 6 and 10.Change from baseline in Functional Assessment of Cancer Therapy–Lung (FACT-L) total scores. The FACT-L is a validated instrument assessing health-related quality of life in patients with lung cancer. It consists of 36 items scored from 0 to 4, with total scores ranging from 0 to 144. The scale includes a general cancer subscale (27 items) and a lung cancer-specific subscale (9 items) (Cella et al., 1995). Higher scores indicate better quality of life. Assessments will be performed at baseline, and at Weeks 6 and 10.Change from baseline in Fear of Cancer Recurrence Inventory–Severity Subscale (FCRI-S) total scores. The FCRI-S assesses the severity of fear of cancer recurrence over the past month (Savard et al., 2023). It consists of 9 items scored from 0 to 4, with total scores ranging from 0 to 36. Higher scores indicate greater fear of cancer recurrence severity, with a score ≥13 generally considered clinically significant (Simard and Savard, 2015). Assessments will be performed at baseline, and at Weeks 6 and 10.Progression-free survival (PFS) and OS in patients with lung cancer. PFS is defined as the time from randomization to the first documented disease progression, based on the Response Evaluation Criteria in Solid Tumors (RECIST) version 1.1 (Bogaerts et al., 2009), or death from any cause, whichever occurs first. OS is defined as the time from randomization to death from any cause.

#### Exploratory outcomes

2.6.3

To systematically investigate the potential mechanisms of action of MSNP granules, biological samples will be collected for analysis. At each study center, the first 20 participants enrolled in each stratification group (with or without concomitant paroxetine use) will be selected, yielding a total of 40 participants per center for mechanistic assessments. Peripheral blood and fecal samples will be obtained at baseline and at Week 6. Fasting venous blood samples will be drawn from the antecubital vein between 8:00 and 10:00 a.m. After standing at room temperature for 1 h, the samples will be centrifuged at 3,000 rpm for 1 min to obtain the supernatant. This will be followed by a second centrifugation at 12,000 rpm for 10 min at 4 °C to isolate serum (Wang et al., 2022). Fecal samples will be collected immediately after morning defecation using sterile containers. All serum and fecal specimens will be stored at −80 °C until further analysis. The following mechanistic indicators will be assessed:Serum inflammatory markers, including interleukin-1β (IL-1β), interleukin-6 (IL-6), C-reactive protein (CRP), and tumor necrosis factor-α (TNF-α), measured using enzyme-linked immunosorbent assay (ELISA).Serum hormones associated with the HPA axis, including adrenocorticotropic hormone (ACTH), corticotropin-releasing hormone (CRH), and cortisol (CORT), also measured using ELISA.Serum neurotransmitters, including dopamine (DA), norepinephrine (NE), and 5-hydroxytryptamine (5-HT), quantified using high-performance liquid chromatography with electrochemical detection.Serum BDNF, measured using ELISA.Serum metabolomic profiles, analyzed through non-targeted liquid chromatography–mass spectrometry.Gut microbiota composition, assessed via 16S rRNA gene sequencing.

### Safety assessment

2.7

Throughout the study period, adverse events (AEs) will be monitored, documented, and managed in accordance with the International Conference on Harmonization-Good Clinical Practice (ICH-GCP) guidelines (Zemsi et al., 2024). AEs are defined as any unfavorable medical occurrence in a participant during the study, including symptoms, signs, diseases, or abnormalities in laboratory test results. Laboratory safety assessments will include routine blood tests and biochemical parameters (hepatic function, renal function, and electrolytes), conducted at baseline and at Weeks 2, 4, 6, and 10. Twelve-lead electrocardiograms will be performed at baseline, Week 4, and Week 10.

All AEs will be coded using the Medical Dictionary for Regulatory Activities (MedDRA) and graded according to the Common Terminology Criteria for Adverse Events (CTCAE), version 5.0, issued by the National Cancer Institute (Spencer et al., 2022). Events of Grade 3 or higher will be classified as serious adverse events (SAEs). All SAEs will be reported to the principal investigator and the institutional review board within 24 h of initial awareness. Appropriate medical management will be provided as required, and all AEs will be followed until resolution, stabilization, or clinical insignificance. Investigators may modify the dosage or discontinue administration of the investigational product at their discretion, based on the severity of the AE and its assessed causality.

The causal relationship between AEs and the investigational product will be assessed using the World Health Organization–Uppsala Monitoring Centre (WHO-UMC) system (Behera et al., 2018). Particular attention will be paid to known adverse reactions associated with paroxetine, such as fatigue, sweating, nausea, decreased appetite, somnolence, dizziness, insomnia, tremor, nervousness, and sexual dysfunction. For MSNP granules, gastrointestinal adverse events including nausea, diarrhea, and abdominal discomfort will be closely monitored. All AEs will be comprehensively documented, including onset time, duration, severity, management, clinical outcome, and their assessed relationship to the investigational product.

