### Blinding

2.12

Trial participants, care providers, outcome assessors, and data analysts will remain blinded to treatment allocation throughout the study. Unblinding will only be permitted in cases of serious adverse events requiring urgent clinical intervention and must be approved by the principal investigator. In all other cases, treatment allocation will remain concealed until completion of the trial and finalization of data analysis. At the end of the 6-week treatment period and before unblinding, blinding assessment will be performed among participants, care providers, and outcome assessors. They will be asked to guess the treatment allocation as “MSNP,” “placebo,” or “uncertain” and to provide the reason for their guess where applicable. The results of the blinding assessment will be summarized descriptively to evaluate the success of blinding.

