### Trial termination criteria

2.16

The trial may be suspended or terminated early if any of the following circumstances occur: (1) unexpected safety risks judged to be related to the study intervention and sufficient to affect participant safety; (2) an unexpectedly high incidence of serious AEs indicating that the overall risk–benefit profile is no longer acceptable; (3) major protocol violations or serious deficiencies in trial conduct that may compromise participant safety, data integrity, or the validity of trial results; (4) failure to achieve adequate recruitment or follow-up despite corrective measures, making the study objectives unattainable; or (5) a decision by the ethics committee, regulatory authority, or data monitoring committee indicating that continuation of the trial is inappropriate. Any decision to suspend or terminate the trial will be documented and reported to relevant parties, and appropriate safety follow-up will be provided for enrolled participants.

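### Seriousness is defined by CTCAE grade (Grade 3 or higher), which conflicts with the ICH-GCP commitment in the same section and mislabels events in both directions

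*Protocol article*

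**What the plan says.** All statements are in the protocol article.

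- Safety assessment (2.7) places the monitoring, documentation and management of adverse events "in accordance with the International Conference on Harmonization-Good Clinical Practice (ICH-GCP) guidelines".
- It defines adverse events broadly, "including symptoms, signs, diseases, or abnormalities in laboratory test results", and schedules blood tests at baseline and Weeks 2, 4, 6 and 10.
- All events are "graded according to the Common Terminology Criteria for Adverse Events (CTCAE), version 5.0". The rule for seriousness follows at once: "Events of Grade 3 or higher will be classified as serious adverse events (SAEs".
- The label then has consequences. In the same section: "All SAEs will be reported to the principal investigator and the institutional review board within 24 h of initial awareness".
- Blinding (2.12): "Unblinding will only be permitted in cases of serious adverse events requiring urgent clinical intervention and must be approved by the principal investigator".
- Interventions (2.4) lists an SAE among the reasons for which the allocated treatment may be stopped or modified.
- Trial termination criteria (2.16), item 2, turns on "an unexpectedly high incidence of serious AEs" that makes the balance of risk and benefit unacceptable. It sets no numerical limit.

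No section makes death, threat to life, hospital admission, disability or medical importance a basis for seriousness. The data items that section 2.7 names for each event include severity and clinical outcome but no separate seriousness item.

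**The concern.** Severity says how intense an event is. Seriousness says what it led to, or could have led to, for the participant. The two overlap but are not the same, and safety reporting rests on the second. Section 2.7 uses the first as if it were the second, a few lines after committing to a standard that keeps them apart.

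Three things are at stake. The first is whether events that the cited standard would call serious reach the principal investigator and the review board within 24 h. The second is whether an event falls within the clauses of the other sections that depend on the SAE label. The third is the meaning of the SAE table at the end of the trial. If SAE simply means Grade 3 or higher, that table repeats the Grade 3 or higher table and tells the reader nothing about outcomes such as admissions.

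**Working it through.** The article states no SAE rate and no SAE threshold, so there is no figure to reproduce. The check is a comparison of rules.

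**Step 1: the two rules.**
- Rule A, stated in section 2.7: an event of CTCAE Grade 3 or higher is an SAE.
- Rule B, implied by the ICH-GCP commitment in section 2.7: an event is serious because of its outcome, whatever its grade. The article names the standard without reproducing its criteria, so this content is a premise brought to the check.

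**Step 2: apply both to every combination of grade and outcome.**

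| CTCAE grade | Serious outcome? | Rule A | Rule B | Agree? |
|---|---|---|---|---|
| 3 or higher | Yes | SAE | SAE | Yes |
| 3 or higher | No | SAE | Not an SAE | No |
| 1 or 2 | Yes | No stated route to SAE | SAE | No |
| 1 or 2 | No | Not an SAE | Not an SAE | Yes |

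The rules part in two of the four cells, in opposite directions. The errors therefore need not cancel, and a similar total would not show that the right events had been labelled.

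**Step 3: the over-inclusive cell.** Laboratory abnormalities count as adverse events, so a Grade 3 value without symptoms or consequences is an SAE under Rule A. Opportunities to observe one: 468 planned participants × 4 post-baseline laboratory visits (Weeks 2, 4, 6, 10) = 1,872 scheduled visits. This is a ceiling on scheduled occasions and not an estimate of events. The safety analysis covers only participants who start treatment, and some visits will be missed.

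**Step 4: the under-inclusive cell.** A Grade 1 or 2 event leading to admission meets no stated SAE criterion. This follows from the absence of any other criterion, since the sentence does not say that only Grade 3 or higher events qualify.

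**Step 5: trace the label.**

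| Section | What depends on the label | Works per event or by count | Affected by |
|---|---|---|---|
| Safety assessment (2.7) | 24 h reporting | Per event | Both cells |
| Blinding (2.12) | Eligibility for unblinding | Per event; also needs urgency and approval | Mainly the under-inclusive cell |
| Interventions (2.4) | One listed reason to discontinue or modify | Per event | Both cells |
| Termination criteria (2.16), item 2 | SAE incidence | Count, judged without a threshold | Both cells |

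The number of events in either disagreeing cell cannot be derived from the article.

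**The case against.** The strongest reply is that the sentence in section 2.7 does not exclude anything. Read with the ICH-GCP reference, the grade rule could be an addition to the standard, so that lower-grade events with serious outcomes would still be SAEs. The article is also a condensed text, and fuller SAE procedures may exist. Part of this stands. A reader might infer that every admission graded 1 or 2 will be missed, and the article does not show that. What remains is that it gives such events no stated route, so nine centres could apply different rules. Even on the additive reading, the over-inclusive cell stays. This is also an explicit rule in the published text and not a detail left out of it.

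Other stronger readings do not hold either:

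- A reader might infer that a distorted SAE count drives reporting and unblinding. Both work event by event. Unblinding also needs urgent clinical intervention and the principal investigator's approval, which an isolated laboratory value would hardly meet. Only termination item 2 uses an incidence. It is a judgement without a threshold, and items 1 and 5 can operate without the SAE label.
- A reader might use an admission for suicidal ideation graded below 3 as the example. The article gives no basis for that grading, and section 2.4 lists severe suicidal ideation separately from SAEs among its reasons. That listing does not supply 24 h reporting.
- A reader might infer that SAE rates would be comparable with no other trial. The supportable statement is narrower: they would not be comparable with trials that define seriousness by outcome. All adverse events are recorded with severity, management and outcome, so the underlying information is not necessarily lost.
- The exclusion criteria remove patients with out-of-range blood tests and those receiving or expecting postoperative cancer therapy. This may make laboratory-only Grade 3 values uncommon. No rate is given either way.

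**Conclusion.** The point holds as a wrongly stated operative rule: section 2.7 decides seriousness by a severity grade and thereby conflicts with the standard it cites. Over-inclusion follows directly from the text. Under-inclusion holds in the limited sense that lower-grade events with serious outcomes have no stated path to SAE status.

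The size is not computable. The documents support only the direction of each error and the four places where the label is used. The conclusion assumes that ICH-GCP treats seriousness as outcome-based and separate from severity, and that no unpublished document overrides the published rule. The primary outcome and its analysis are unaffected. Confidence is high on the conflation and lower on how often it would change the handling of an event.

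**What to change.** 1. In section 2.7, replace the grade-based sentence with a definition of SAEs by the outcome-based seriousness criteria of the cited ICH-GCP standard, stated in full and independent of CTCAE grade.
2. Keep CTCAE version 5.0 as the severity scale only.
3. Add a seriousness field to the adverse event form, recorded separately from grade.
4. Tabulate SAEs and Grade 3 or higher events as two separate counts by arm.
5. Make Interventions (2.4), Blinding (2.12) and Trial termination criteria (2.16) refer to the corrected definition, so that one meaning of SAE applies throughout. The clinical rules in those sections are for the sponsor to reconcile, and this point proposes no change to them.

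The cost is small: one sentence, one form field and aligned cross-references. It cannot be assumed that this precedes recruitment. The article is dated 19 June 2026, and Trial status (2.15) anticipates a start in that month. If enrolment has begun, the change is an amendment, and events already recorded must be reclassified against the new criteria.

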### Participant timeline

2.8

The trial will last for 11 weeks, consisting of a 1-week screening period, a 6-week treatment phase, and a 4-week post-treatment follow-up. The timeline for participant enrollment, intervention delivery, and outcome measurements is outlined in Figure 3.

**FIGURE 3 F3:**
[figure not shown]
Schematic representation of participant inclusion, therapeutic interventions, and scheduled assessments. BDNF, brain-derived neurotrophic factor; FACT-L, Functional Assessment of Cancer Therapy–Lung; FCRI-S, Fear of Cancer Recurrence Inventory–Severity Subscale; GAD-7, Generalized Anxiety Disorder-7; HAMD-17, 17-item Hamilton Depression Rating Scale; HPA, hypothalamic-pituitary-adrenal; MSNP, modified Sini Powder; OS, overall survival; PHQ-9, Patient Health Questionnaire-9; PFS, progression-free survival; PSQI, Pittsburgh Sleep Quality Index.

### Sample size estimation

2.9

Previous clinical studies have shown that SNP, either alone or in combination with antidepressants, may help alleviate depressive symptoms. For example, a randomized, double-blind, placebo-controlled trial in breast cancer patients with mild to moderate depression showed that SNP significantly reduced HAMD-24 scores compared with placebo, with a greater reduction in the SNP group than in the placebo group (4.46 ± 4.403 vs. 0.66 ± 4.463, *P* < 0.001) (Hong et al., 2026). Another randomized trial, in which effectiveness was defined as a ≥25% reduction in the HAMD-17 total score from baseline, showed that SNP combined with fluoxetine improved the total effective rate in adolescents with depression compared with fluoxetine alone (95.12% vs. 77.50%, *P* < 0.05) (Zhang et al., 2023). These studies provide specific clinical evidence supporting the potential antidepressant effects of SNP.

The sample size was calculated based on the primary outcome, namely, the total effective rate at the end of the 6-week treatment period. Considering that concomitant use of antidepressants may affect treatment response, a stratified design was adopted, and sample sizes were estimated separately for the two strata: participants without paroxetine use and participants with paroxetine use. Because individual clinical trials differed from the present study in population characteristics, disease context, and intervention setting, the formal assumptions for sample size estimation were not directly derived from a single clinical trial. Instead, they were primarily based on the pooled effect estimates from a previous meta-analysis of traditional Chinese medicine for depression, which provided more robust parameter estimates (Wang et al., 2019).

According to this meta-analysis, in the non-paroxetine stratum, the expected total effective rates were 59.6% for MSNP alone and 37.0% for placebo alone, corresponding to a projected risk ratio of 1.61. In the paroxetine stratum, the expected total effective rates were 91.6% for MSNP plus paroxetine and 79.0% for placebo plus paroxetine, corresponding to a projected risk ratio of 1.16. Using the “Tests for Two Proportions” module in PASS version 21, with a two-sided alpha of 0.05, 80% power, equal allocation within each stratum, and an assumed dropout rate of 15%, the required sample sizes were 180 participants for the non-paroxetine stratum and 288 participants for the paroxetine stratum. Therefore, the final total sample size was set at 468 participants. In the non-paroxetine stratum, 90 participants will receive MSNP alone and 90 will receive placebo alone. In the paroxetine stratum, 144 participants will receive MSNP plus paroxetine and 144 will receive placebo plus paroxetine. Overall, 234 participants will receive MSNP-containing interventions (intervention group), and 234 participants will receive the corresponding placebo-containing control interventions (control group).

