All statistical analyses will be performed using SPSS version 26.0 and R version 4.3.1. A two-sided p-value ≤ 0.05 will be considered statistically significant for the primary outcome. No adjustment for multiplicity is planned for secondary outcomes, and these analyses will be regarded as exploratory. No interim analyses are planned for this trial.

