## Discussion

3

This study is a nationwide, multicenter, randomized, double-blind, placebo-controlled clinical trial designed to systematically evaluate the efficacy, safety, and potential mechanisms of MSNP in the treatment of postoperative mild-to-moderate depression in patients with NSCLC. The trial is based on a rigorous methodological design, integrating multidimensional efficacy assessments and omics-based mechanistic analyses. It aims to address the current lack of high-quality clinical evidence for TCM interventions in depression.

Grounded in real-world clinical practice, this study adopts a design that ensures both scientific rigor and clinical applicability. First, it employs a strict randomized, double-blind, placebo-controlled design and is conducted collaboratively across nine research centers in different provinces of China, ensuring strong external validity and generalizability. Second, the study stratifies participants based on concomitant paroxetine use, with the aim of achieving two key objectives. The first is to evaluate the efficacy and safety of MSNP monotherapy as a viable alternative for patients who are unwilling or unable to tolerate antidepressants. The second is to explore the potential synergistic effects or mitigation of side effects when MSNP is combined with standard pharmacotherapy. This dual-scenario design enables a comprehensive appraisal of MSNP’s clinical value in personalized treatment strategies. In addition, the study includes multidimensional efficacy endpoints covering depression, anxiety, sleep disturbance, fear of recurrence, quality of life, and cancer survival. Multiple timepoint assessments are used to capture the psychological and physiological effects of MSNP in a comprehensive manner.

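### The stated 80% power belongs to two separate stratum tests, not to the single primary comparison that is declared, and the model leaves open which contrast that comparison is

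*Protocol article*

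**What the plan says.** Section 2.9 (Sample size estimation) treats each stratum as its own two-group problem: "sample sizes were estimated separately for the two strata: participants without paroxetine use and participants with paroxetine use". The design parameters are given once and applied in each stratum: "with a two-sided alpha of 0.05, 80% power, equal allocation within each stratum, and an assumed dropout rate of 15"%. The assumed effects differ. Without paroxetine, "the expected total effective rates were 59.6% for MSNP alone and 37.0% for placebo alone"; with it, "the expected total effective rates were 91.6% for MSNP plus paroxetine and 79.0% for placebo plus paroxetine". The outcome is that "the required sample sizes were 180 participants for the non-paroxetine stratum and 288 participants for the paroxetine stratum", followed by "Therefore, the final total sample size was set at 468 participants".

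Section 2.14 (Statistical analysis) describes one primary analysis. It is a log-binomial model for the total effective rate that yields one adjusted risk ratio for intervention against control, with centre and paroxetine use as covariates and a treatment-by-paroxetine interaction in the same model. There is one decision rule: a two-sided p-value of 0.05 or less "will be considered statistically significant for the primary outcome". Multiplicity is mentioned only for secondary outcomes.

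The Discussion says that stratification was adopted "with the aim of achieving two key objectives": to evaluate MSNP alone for patients who will not or cannot take antidepressants, and to explore synergy or fewer side effects when it is added to standard drug treatment.

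**The concern.** The sizing answers two questions and the analysis answers one. A reader who takes 80% as the power of the primary test is misinformed, because that figure was calculated for a different test.

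The interaction term makes this worse. With it in the model there is no single treatment coefficient that means the overall effect. Under reference coding, the coefficient printed for treatment is the effect in whichever stratum is the reference. The p ≤ 0.05 rule could then be read as applying to the overall effect, to MSNP alone, or to MSNP plus paroxetine. These are different claims with different power. If the choice is still open when results are seen, the results can steer it.

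**Working it through.** **Inputs.** From section 2.9: rates 59.6% vs 37.0% and 91.6% vs 79.0%; two-sided alpha 0.05; power 80%; 1:1 allocation; dropout 15%; 90 and 144 per arm.

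**1. Reproduce 468.** Two-proportion formula, pooled variance, no continuity correction, with p̄ the mean of the two rates:

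n per arm = [1.96·√(2p̄(1−p̄)) + 0.8416·√(p1(1−p1) + p2(1−p2))]² / (p1−p2)²

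- Non-paroxetine: (1.385 + 0.579)² / 0.226² = 75.6, so 76. 76/0.85 = 89.4, so 90 per arm and 180 in total. Exact match.
- Paroxetine: (0.982 + 0.415)² / 0.126² = 122.8. 122.8/0.85 = 144.5, which is 144 or 145 per arm by rounding, so 288 or 290. The gap of two is rounding, not an error.

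The figures fit stand-alone stratum tests.

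**2. Power within strata after dropout.** 90 × 0.85 = 76.5 and 144 × 0.85 = 122.4. With 76 and 122 per arm, power is 80.2% and 79.7%. This is the stated 80%.

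**3. Power of the overall test, same numbers.**

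- Log risk ratio, inverse-variance weights. The variance in a stratum is the sum over arms of (1−p)/(pn).
  - Non-paroxetine: 0.404/(0.596·76) + 0.63/(0.37·76) = 0.0313; log(0.596/0.37) = 0.477.
  - Paroxetine: 0.084/(0.916·122) + 0.21/(0.79·122) = 0.00293; log(0.916/0.79) = 0.148.
  - Weights 31.9 and 341.2, so about 9% and 91%.
  - Pooled log RR = (31.9·0.477 + 341.2·0.148)/373.2 = 0.176 (RR 1.19); SE = 1/√373.2 = 0.0518; z = 3.40; power Φ(3.40 − 1.96) = 93%.
- Stratified risk difference: (76·0.226 + 122·0.126)/198 = 0.164; SE 0.0409; z = 4.02; power 98%. A simulated Cochran-Mantel-Haenszel (CMH) test also gives 98%.
- Crude comparison ignoring strata: 95%. With all 468 evaluable, the range is about 96% to 99%.

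**4. The model with the interaction.**

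- Treatment coefficient under reference coding: 0.477/√0.0313 = 2.69 gives 77% (non-paroxetine reference); 0.148/√0.00293 = 2.73 gives 78% (paroxetine reference).
- The interaction itself: (0.477 − 0.148)/√(0.0313 + 0.0029) = 0.329/0.185 = 1.78; power Φ(1.78 − 1.96) = 43%. The ratio of risk ratios is 1.39.

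**5. What two stratum tests would imply, if someone adopted them.** Either may be claimed: 1 − 0.95² = 9.75% familywise error when neither stratum has an effect. Both must succeed: 0.802 × 0.797 = 64% power. The article declares neither rule.

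**6. Stratum tests only after a significant overall test.** Simulated with a CMH overall test, 76 and 122 per arm, each stratum at 0.05:

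- No effect anywhere: the chance of any stratum claim is 3.3%, so no Holm step is needed for two strata.
- Effect only without paroxetine: the chance of that claim falls from 79% to 47%.
- Effect only with paroxetine: it falls from 80% to 45%.

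This cost depends on the weighting. With the log-RR weights of step 3 and an effect only without paroxetine, the paroxetine variance is 2·0.21/(0.79·122) = 0.00436 (weight 229.5). The overall z is then (31.9·0.477)/√(31.9 + 229.5) = 0.94, so the overall test passes only about 15% of the time. With an effect only with paroxetine, the other variance is 2·0.63/(0.37·76) = 0.0448 (weight 22.3), z = (341.2·0.148)/√363.5 = 2.65, and it passes about 75% of the time.

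**The case against.** The best defence is that nothing harmful has been declared. Section 2.14 gives one comparison and one threshold. Sizing each stratum to be informative and then analysing them together is conservative, and section 2.9 gives a reason: antidepressant use may change response. A sample size calculation spends no alpha; only a declared test does. The article is also condensed, and an order for stratum follow-up tests is commonly left to the analysis plan.

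Most of this stands. A reader might infer that stratum claims carry about 10% error. The documents do not support that as a statement about this trial: it needs both strata tested at 0.05, either result claimable, and no effect in either. Each single stratum test would still be at 5%. The 64% likewise needs a both-must-succeed rule that appears nowhere. Nor does the Discussion set up two confirmatory hypotheses. Its first objective is a stratum efficacy question, but its second is worded as exploration of synergy and side effects.

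Two things are not answered. Section 2.9 still reports a power that is not that of the test in section 2.14. And the interaction sits in the primary model as described, so the ambiguity comes from what the article says and not from what it leaves out.

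**Conclusion.** The point holds as a mismatch between sizing and analysis, plus an unfixed primary contrast. The stated 80% is within-stratum power. The overall comparison has about 93% (log risk ratio) to 98% (risk difference or CMH) after 15% dropout. If the treatment coefficient of the interaction model were used instead, power would be about 77% to 78% and the claim would concern one stratum only.

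It would be wrong to conclude that the trial is underpowered or that its declared type I error is inflated. At the assumed rates the overall test has more than the power stated, at 0.05.

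These figures rest on the rates in section 2.9, on dropout acting as a plain loss of 15% of participants, and on large-sample approximations without centre effects. The contrast should be settled before recruitment, which section 2.15 expects to start in June 2026.

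**What to change.** Keep 468 and change the wording.

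- **Section 2.14:** state that the single primary test is the overall treatment effect adjusted for centre and paroxetine use, at two-sided 0.05. Take it from the model without the interaction, or from a marginal contrast whose stratum weights are stated. Fit the treatment-by-paroxetine interaction as a separate secondary analysis, and note its power of about 43%.
- **Section 2.9:** restate power as about 93-98% for the overall test, with the figure for the weighting chosen, and about 80% for each stratum at 0.05.
- **Stratum effects:** either label them supportive, or test each at 0.05 only if the overall test is significant. Holm is not needed for two strata behind that condition.

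The cost is wording, with no extra participants, plus one real trade-off. If MSNP works in only one stratum, requiring the overall test first lowers the chance of that stratum's claim from about 80% to about 45-47% under CMH weighting. Under log-risk-ratio weighting the loss falls mostly on MSNP alone (overall test passed about 15% of the time) and little on the combination (about 75%). If the monotherapy question matters most, that should inform the choice of weighting. Labelling the stratum effects supportive avoids the trade-off but gives up a confirmatory stratum claim.
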